**Proximal outcomes**:**												

PERSONAL DETERMINANTS												

Taste preferences	Liking of FV and number of different FV liked	X										X

Dietary knowledge	Knowledge of national FV recommendations	X										

Awareness	Awareness of whether they meet national recommendations	X										X

Short term outcome expectations	Perceived immediate effects of eating FV: e.g. more energy, feel better, FV not filling enough, FV allergy	X										

**Potential positive side effects:**											X	

More energy	Loss of energy during the school day	X			X						X	

School concentration	Unable to concentrate during class lessons	X			X						X	

Wellbeing	Children's level of life satisfaction, if they most of the time are feeling well and full of energy	X			X							

Usual intake of unhealthy food	Intake of soft drinks, sweets and salty snacks (FFQ)	X										

School: environmental changes	Nutrition policies, FV programme, food availability		X			X						

**Unintended adverse outcome:**											X	

Bullying	How often they have been bullied at school in the past couple of months	X										

Weight- and eating related teasing	If class mates are teasing each other because of weight, lunch bags or eating habits	X										

School class thriving	If pupils in their class enjoy being together	X										

Free FV replace FV eaten at other times of the day**	Eating less FV at home (24-hour recall questionnaire). Fewer children bringing FV to school from home	X	X								X	

**Moderators:**												

Socioeconomic position	Parent occupational social class	X	X									

Socioeconomic position	Parental education		X									

Gender	Boys and girls	X										

Implementation degree	Dose delivered/received, fidelity: adherence to protocol	X	X	X	X	X	X	X	X	X	X	X

**Abbreviations: **CT = Computer tailoring, FG = focus groups with children and/or teachers, FV = fruit and vegetables, PE = process evaluation, * at intervention schools only, **measured for fruit and vegetables separately

#### Measures

The primary outcomes measures were corresponding to the distal outcomes in the programme theory and measured by two pupil-reported measures at all three time points:

*Total fruit-, vegetable-and FV intake in grams per day *(in school + outside school) measured by the validated Pro Children pre-coded 24-hour recall questionnaire [77]. The 24-hour recall questionnaire measured how many pieces or portions of specific types of FV the pupils had consumed in five different time intervals on the previous day: before school, at school, after school, at dinner and after dinner. Pieces and portions of FV were converted into grams based on food weights applied by experts in the field [77,80]. The vegetable measure excluded potatoes. The fruit measure included 100% natural juice but juice was only counted as one portion/100 grams a day regardless of the number of glasses consumed. **Pre-specified success indicator: **Based on the effect size obtained in the Pro Children study [21], we aimed at a 20% increase in FV intake at intervention schools at 1^st ^follow-up versus baseline and control school. This increase should be maintained into 2^nd ^follow-up.

*Habitual fruit-, vegetable-, and FV intake *was measured by the validated Pro Children food frequency questionnaire (FFQ) [77]. Fruit intake was measured by one item on fresh fruit. Vegetable intake was measured by three separate items: salad or grated vegetables, other raw vegetables, and cooked vegetables. **Pre-specified success indicator: **Significantly higher proportions of pupils eating FV daily at intervention schools at 1^st ^follow-up. This increase should be maintained into 2^nd ^follow-up.

Secondary outcomes were measured at all three time points and included 1) targeted determinants, corresponding to the proximal outcomes in the programme theory such as taste preferences, availability, and perceived parental barriers for serving FV at home and explorative outcomes, corresponding to intended and unintended side-effects such as wellbeing and eating-related teasing,

#### Proximal outcomes of the intervention: Changes in determinants

Environmental, social and personal determinants were measured by questionnaires to pupils, parents, principals and representatives from sports-and youth clubs. The intervention programme was designed to create significant, positive changes in specific determinants of teenagers' FV consumption at intervention schools at 1^st ^follow-up versus baseline and control schools. As shown in Table 4 the Boost study is characterised by thorough measures of both perceived and actual social and environmental influences (e.g. parental intake and home availability) using different data sources. We also measured potential confounders of the association between intervention and FV intake (determinants of FV intake which the intervention was not tailored to) such as school nutritional policies, family meal habits, family structure, and ethnic background (not shown in Table 4). Parental SEP (moderator in Figure 1) will be based on questions to parents and pupils on each parent's educational and occupational background.

*Predefined explorative secondary outcomes: changes in positive and negative intended and unintended side-effects*: Intended positive side effects and unintended adverse effects will be measured by questionnaires to the pupils and parents. We will assess whether there are significant changes in these among pupils at intervention schools versus baseline and control group.

Intended positive side-effects: At follow-up, the increased access to FV at intervention schools was expected to significantly decrease proportions of pupils at intervention schools who felt out of energy, had difficulties in concentrating during class in school and who ate unhealthy food almost daily. Also, we expected significant positive changes in pupils' well-being. By use of questionnaires to the school principals, we will measure whether participation in the Boost project has initiated some environmental changes and capacity building at the intervention schools at 2^nd ^follow-up (e.g. initiation of FV programmes, increased sale of FV in schools, increased focus on school food policies or limiting pupils' access to unhealthy food at school).

Unintended adverse effects: It will be evaluated whether the intervention and the increased focus on healthy eating has produced a significant increase in weight-and eating-related teasing or bullying. There is a risk that the free FV in school only replace FV eaten at other times of the day which will hinder an effect on the pupils' total intake of FV [22]. We will therefore analyse whether fewer adolescents eat FV at home and bring FV to school from home after the intervention. As unintended adverse effects are difficult to predict they will also be illuminated through qualitative interviews with pupils and teachers as part of process evaluation (see Table 4).

#### Planned statistical effect analyses

The primary aim of the effect evaluation will be to assess whether our goal of a 20% increase in FV intake has been achieved. All further impacts of the intervention such as intended proximal effects (determinants) and unintended positive and negative side effects will also be subject to evaluation. Outcomes will be analysed after the principle of intention-to-treat including all pupils in the arm to which they were allocated whether or not they received (or completed) the intervention given to that arm. These results will be compared to per protocol analyses of pupils at schools that complied sufficiently with the intervention manual to exhibit the effect of treatment at the individual level. Descriptive analyses will be used to calculate the net effect of the intervention ((follow-up intake_intervention _-baseline intake_intervention_) -(follow-up intake_control_-baseline intake_control_)). The effect of the multicomponent intervention will be analysed for each and all six primary outcome measures of FV intake. To account for the cluster-design and repeated measurements, changes in consumption from baseline to first-and second follow-up will be analysed by multilevel multivariate regression analyses. All analyses will be stratified by gender and we will examine if the intervention have differential effects on FV intake among pupils from low and high social class. Our hypothesis is that the intake of teenagers from low income families at school will benefit more from the free FV provision than their peers from high income families as they may not usually bring FV from home.

In another analysis implementation degree (high/medium/low) will be included as we hypothesise that adolescents at schools/school classes who have been exposed to a large dose of the intervention will have a higher intake at 1^st ^follow-up compared to adolescents at schools where the intervention has not been fully implemented.

In a third analysis we will try to examine if it is possible to decompose the effects of the different intervention components through mediation analysis. We will analyse the effect of the different intervention components on the determinants (proximal outcomes) they have been tailored to. One hypothesis is for example that pupils at intervention schools will like a larger variety of FV than the pupils at control schools at 1^st ^follow-up due to the free FV provision. In a second analytical step we will examine if change in intake is preceded by change in determinants through mediation analyses.

Parent non-response at baseline and pupil and parent attrition between baseline and 1^st ^and 2^nd ^follow-up will be analysed by multilevel analyses using data from pupil baseline survey and national registries.

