#### Programme theory and outcomes

The programme theory (Figure 1) was guided by systematic reviews of determinants of adolescents' FV intake, reviews of intervention studies, theory, experiences from recent successful or innovative intervention studies, especially the international Pro Children study and the Norwegian Health In Adolescents (HEIA) study [3,6,39,55-57], input from the planning group and international steering committee, and discussions with the target group. In agreement with best practice, the programme theory outlined the causal chain which explains how the intervention is expected to impact distal outcomes (FV intake) through changes in proximal outcomes (determinants). We conducted a brainstorm and prioritisation of important and changeable determinants of adolescents' FV consumption identified from systematic literature reviews [3,6]. As shown in Figure 1 the intervention was designed to produce changes in environmental, social and personal determinants. We hypothesised that the effect would differ by gender and SEP because of the low FV intake among boys and low income children [3]. Likewise we hypothesised that the effect of the intervention would differ by implementation degree.

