#### Power calculations

To assess the adequate sample size of schools and pupils needed to detect a 20% difference between intervention-and control schools in intake of FV at follow-up, we calculated the power of a two-sample *t*-test using the SAS computer code suggested by Donner & Klar (1996) [75]. We based intra-class correlations (= 0.01) on Pro Children data. If 20 schools with two school classes of 20 pupils each were randomly assigned to each intervention group, the analyses showed that there would be more than 90% power to detect a 20% increase in pupils' mean intake of FV between intervention-and control schools (N schools = 40, N pupils = 1,600).

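### The plan stratifies every analysis by gender without fixing the role of the all-pupil comparison, and it plans no test of its own hypothesis that the effect differs by gender

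*Protocol article*

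**What the plan says.** The article sizes the trial on boys and girls together. Under Power calculations it seeks the sample "needed to detect a 20% difference between intervention-and control schools in intake of FV at follow-up", with "N schools = 40, N pupils = 1,600", and concludes that "there would be more than 90% power to detect a 20% increase in pupils' mean intake of FV between intervention-and control schools".

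Planned statistical effect analyses first sets out the primary aim (the 20% goal), an intention-to-treat set of all allocated pupils, a net-effect formula and a multilevel model. None of these has a gender split. It then says: "All analyses will be stratified by gender and we will examine if the intervention have differential effects on FV intake". The rest of that sentence limits the differential-effect examination to pupils of lower and higher social class, and the hypothesis that follows it is also about family income.

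Programme theory and outcomes says: "We hypothesised that the effect would differ by gender and SEP because of the low FV intake among boys and low income children". Table 4 lists gender among the moderators, beside socioeconomic position and implementation degree.

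**The concern.** Two things are left open or missing.

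First, a rule covering all analyses makes no exception for the primary one. The reader cannot tell whether the 20% goal will be judged on all pupils, on boys and girls separately, or on some combination. The section names six primary outcome measures, so a fully stratified reading gives 2 × 6 = 12 gender-specific results at each follow-up, with no statement of which one decides.

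Second, the gender hypothesis has no test. An estimate for boys and an estimate for girls, each set against zero, do not show whether the two effects differ. A significant result in one gender and not in the other can easily arise when the true effects are equal. Because the authors expect a gender difference, such a pattern could be taken as confirmation.

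**Working it through.** **Inputs.** Power calculations uses a t-test for two groups that allows for clustering and an ICC of 0.01 taken from the Pro Children study. On the design it says: "If 20 schools with two school classes of 20 pupils each were randomly assigned to each intervention group". That makes 40 pupils per school and 20 schools per arm. The section gives no SD, significance level or sidedness. I assume two-sided 0.05 and use the baseline values of Table 5, averaged over arms (mean, SD in g/day):
- total intake: 365.1, 262.5
- fruit including juice: 229.3, 196.6
- vegetables: 135.8, 161.8

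Table 5 shows about 52% boys in each arm, so one gender is taken as m = 20 pupils per school.

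**Formulas.** Design effect = 1 + (m − 1) × ICC. Effective n per arm = 20m / design effect. SE = SD × √(2 / effective n). Power comes from a noncentral t on 38 df with noncentrality (0.20 × mean) / SE.

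**The plan's own figure.** All pupils, m = 40: design effect 1 + 39 × 0.01 = 1.39; effective n 800 / 1.39 = 576. For total intake, SE = 262.5 × √(2/576) = 15.5 g; the difference is 0.20 × 365.1 = 73.0 g; noncentrality 4.72; power 99.6%. This is consistent with the stated figure of more than 90%.

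**One gender.** m = 20: design effect 1 + 19 × 0.01 = 1.19; effective n 400 / 1.19 = 336. Effective n falls by 42% rather than 50%, because the design effect also falls. SE = 262.5 × √(2/336) = 20.2 g; noncentrality 3.61; power 94%.

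**If boys and girls had the same true effect.** Both estimates come from the same 40 schools, so they are correlated. With a common school effect, the correlation between the boys' and girls' means in a school is 0.01 / (0.01 + 0.99/20) = 0.17. I simulated school means under this model with a 20% effect in both genders, used a t-test on school means within each gender, and counted how often exactly one was significant.

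| Outcome (ICC 0.01) | Power, all pupils | Power, one gender | Exactly one gender significant |
|---|---|---|---|
| Total intake | 99.6% | 94% | 11% |
| Fruit | 97% | 84% | 25% |
| Vegetables | 79% | 56% | 44% |

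**Sensitivity.** At an ICC of 0.05, which is my assumption and not in the article, power goes from 88% to 78% for total intake and from 48% to 38% for vegetables. The chance of exactly one significant gender becomes 24% and 32%. Table 5 excludes 274 of 2,156 pupils as over-eaters. If they were kept, with an assumed mean of 1,200 to 1,500 g and SD of 300 g among them, total-intake power at ICC 0.01 (normal approximation) would be 96 to 99% pooled and 81 to 89% in one gender.

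**What an interaction test could show (total intake, normal approximation).** If the school effect is common to both genders, it cancels from the boy–girl contrast: SE = √(4 × 0.99 × 262.5² / 400) = 26.1 g. A difference between the genders' effects of 20% of the mean (73.0 g) gives 73.0 / 26.1 = 2.80, power about 80%. A difference of 10% (36.5 g) gives 1.40, about 29%. If nothing cancels, SE = √2 × 20.2 = 28.6 g, and power is about 72% (73% on the control-arm mean) and 25%.

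**The case against.** The strongest reply is that the pooled analysis was never dropped. The primary aim, the intention-to-treat set and the net-effect formula all concern pupils overall, and stratifying by gender can mean showing every result by gender as well. That stands. A reader might infer that the strata replace the powered comparison, but the text does not say so. What it leaves unfixed is how the two relate.

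It also stands that the power claim is not broken. For total intake each gender keeps about 94% at the article's ICC. The article does not claim power for vegetables alone, and even the pooled figure there is only 79%, so part of that shortfall owes nothing to stratification.

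A reader might also put the risk of discordant results higher by treating boys and girls as independent. At ICC 0.05 that gives 34% for total intake and 47% for vegetables. Pupils in the same schools are not independent, and the shared school effect brings these down to 24% and 32%. Nor does the article announce that it will read discordant p-values as a gender difference.

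Finally, the Background and Discussion mention effect-modification analysis for low-intake groups, boys included, and an article may leave the exact model term to the full analysis plan. This answers only part of the point. Those mentions are general, whereas the sentence that does fix the analysis gives gender stratification only and reserves the differential-effect examination for social class.

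**Conclusion.** The point holds in two parts. The role of the gender strata relative to the all-pupil comparison is not fixed, and the stated gender hypothesis has no test in the planned analyses. The second part rests on the text alone and needs no numerical assumption.

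The practical size depends on the outcome. It is small for total intake, where one gender still has ample power and discordance by chance is about one in nine. It is material for fruit (about one in four) and for vegetables (more than two in five). These figures rest on ICC 0.01, baseline SDs without over-eaters, equal numbers of boys and girls per school, a school effect common to both genders, and a two-sided 0.05 level that the article does not state. They do not support a claim that the trial loses its powered answer, or that a spurious gender finding is likely on total intake.

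**What to change.** State that the all-pupil multilevel comparison decides whether the 20% goal is met. Test the gender hypothesis with a gender-by-arm interaction in that same pooled model. Report the interaction estimate with its confidence interval, because its power is modest and a non-significant result would not show equal effects. Present the boys' and girls' estimates beside it as subgroup description, not as separate verdicts on the primary aim.

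The cost is one model term and a change of wording. No extra data are needed and every gender-specific result is kept.

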#### Baseline data collection

Pupils completed internet-based questionnaires in class and brought home questionnaires for their parents to complete. As fathers and mothers may influence their children's food habits differently [81], both parents were invited to complete questionnaires. At all schools, trained project staff helped teachers carry out the surveys. The year 7 pupils received standardised oral instructions and a factsheet with definitions and photos of portion sizes. During the baseline visit, observations and photo documentation were made of the school food environment such as presence of canteen or fruit tuck shop, and classroom conditions. A pupil or teacher in each class was briefly interviewed about lunch habits among classmates and unwritten school rules. All principals completed an electronic questionnaire on structural, physical and social characteristics of their school. Pupil, parent and principal surveys and observations will be repeated at 1^st ^and 2^nd ^follow-up.

In January 2011, managers and coaches of clubs and teams were asked to complete internet-based baseline surveys on availability of FV and unhealthy food and existence of policies before receiving Boost information material. A 1^st ^follow-up was carried out in September/October 2011.

#### Response rates and characteristics of pupils at baseline

As shown in Figure 2, response rates were high (> 94%) among both pupils and school principals at intervention-and control schools. A few pupil questionnaires were excluded from the baseline data file because of lack of parental consent. Only three pupil questionnaires were unserious and therefore excluded. The parental response rate was lower in both groups, but higher at intervention schools. Most of the returned parent questionnaires (60%) were completed by female caretakers. The response rates among coaches and managers of sports and youth-clubs were good (> 60%).

Baseline characteristics of pupils from intervention-and control schools were compared by chi-square tests for proportions and *t*-tests for continuous variables to verify the adequacy of the randomisation procedure. The baseline data file included 1,121 pupils from intervention schools and 1,035 pupils from control schools. There were no significant socio-demographic and outcome differences between intervention-and control groups at baseline except for a significant larger percentage of pupils at control schools reporting their parents to be born in Denmark (Table 5). Forty percent of the pupils reached the WHO recommendations of daily FV intake and one fifth accomplished the national recommendations. Less than half of the pupils consumed fruit daily and only one fifth of the pupils consumed raw vegetables daily. The proportions of pupils having access to FV at home, in school and leisure time were almost similar in the two samples at baseline (Table 6). One fifth of the pupils did not attend a sports-or youth club.

**Table 5 T5:** Baseline characteristics of pupils at intervention-and control schools: socio-demographics and primary outcome measures (significant differences are highlighted in bold, p < 0.05)

	Intervention sample (N = 1,121)		Control sample (N = 1,035)		
**Sociodemographics**	**Percentage (N) of pupils reporting the given characteristic**	**N Missing**	**Percentage (N) of pupils reporting the given characteristic**	**N Missing**	**P-value from chi-square test or *t*-test**

Boys	51.8% (581)	0	51.9% (537)	0	p = 0.980

Mother is unemployed*	12.0% (134)	6	10.5% (108)	1	p = 0.169

Father is unemployed*	6.8% (73)	6	5.3% (53)	1	p = 0.237

Mothers' SEP*	26.7% (295)	6	27.9% (286)	2	p = 0.198
High (I + II)	26.7% (295)		29.9% (307)		
Medium (III + IV)	23.9% (264)		21.8% (223)		
Low (V + 7)	22.7% (251)		20.4% (209)		
Other (6 + 8)					

Fathers' SEP*	20.1% (218)	6	18.9% (189)	2	p = 0.319
High (I + II)	37.8% (411)		41.4% (415)		
Medium (III + IV)	18.9% (205)		16.7% (167)		
Low (V + 7)	23.2% (252)		23.0% (230)		
Other (6 + 8)					

Pupil was born in Denmark	95.1% (1060)	6	95.0% (983)	0	p = 0.988

Mother was born in Denmark	**83.4% (930)**	6	**86.1% (891)**	0	**p = 0.035**

Father was born in Denmark	**84.1% (938)**	6	**88.3% (914)**	0	**p = 0.006**

Speaking Danish at home	95.7% (1068)	6	96.2% (996)	0	p = 0.597

